### Anthropometric and laboratory assessments

Anthropometric and laboratory evaluations were conducted as part of the study protocol. Trained physicians performed subject interviews to elicit medical history, medication usage, and alcohol consumption habits. Afterward, anthropometric measurements were taken while subjects were attired in lightweight garments and shoeless. These measurements included height, weight, waist circumference (WC), and hip circumference (HC). Body Mass Index (BMI) was then computed using the individual's weight divided by the square of their height (kg/m^2^). Laboratory assessments were evaluated by obtaining serum samples after an overnight fast and were as follows: ALT, AST, γ-GTP, Tc, Triglyceride, HDL-c and LDL-c.

### B-mode US

For each participant, B-mode US examination was performed using a US system (RS 85, Samsung Medison, Co. Ltd.) with a convex probe (CA1-7A). All participants were requested to fast for at least 8 h before the US examinations. Hepatic steatosis will be graded subjectively by the operator as no steatosis, mild steatosis, moderate steatosis, severe steatosis. They were be graded based on the following findings: (1) higher echogenicity of the liver, (2) impaired visualization of the intrahepatic vessels, and (3) impaired visualization of the diaphragm and posterior right hepatic lobe due to ultrasound beam attenuation (21).

### QUS techniques

The QUS technique was utilized to evaluate each participant in this study. A US system with a convex probe was used to conduct the QUS analysis (RS 85, Samsung Medison, Co. Ltd.). Two QUS parameters, namely AC-TAI and SC-TSI, were calculated from the RF data using an inhouse program developed in MATLAB R2015a (MathWorks, Inc.). The color-coded maps of both AC-TAI and SC-TSI were produced by analyzing the RF data of the corresponding B-mode images.

To determine the TAI and TSI maps of the liver parenchyma, one researcher carefully placed ROIs (approximately 2 cm in inner arc length and 4 cm in height) on the B-mode images while avoiding large vessels, focal lesions, and reverberation artifacts under the liver capsule. In cases where blood vessels were unavoidable, the areas containing large vessels were excluded from the calculation of AC-TAI and SC-TSI, which resulted in vacant regions on the TAI and TSI maps. The MRI-PDFF results were unknown to the researchers when measuring the QUS parameters. The five measurements for each examination were averaged for each QUS parameter.

### CAP

The assessment of hepatic steatosis in the present study was carried out using FibroScan® (Echosens, Paris, France), with X- or XL-probes employed to capture the CAP in dB/m. The examination process involved instructing all participants to fast for a minimum of 6 h before assuming a supine position with their right arm in maximal abduction. The technique entailed scanning the right liver lobe through an intercostal space and aiming to obtain ten successful acquisitions from each subject. Trained operators executed the transient elastography while remaining masked to data and participant diagnoses. The final CAP score (dB/m) was derived from the median of individual measurements, with the quartile spacing of CAP not exceeding 40 dB/m.

### MRI

All participants underwent liver MRI using chemical shift encoding. To measure proton density fat fraction (PDFF), the researchers employed complex-based chemical shift-encoded water-fat reconstruction techniques with six two-dimensional gradient-recalled-echo images, an imaging matrix of 256 × 192, and a 3 mm slice thickness. A low flip angle (4°) was used to minimize the T1 bias between fat and water. The PDFF maps were reconstructed automatically using the vendor's algorithm with T2* correction calculated from signal decay and a multi-peak fat model. For each patient, one experienced radiologist, blinded to the other test and examination results, manually demarcated the whole liver boundary of the PDFF map. The section chosen to demarcate need avoid large vessels and focal lesions as far as possible. The average of ROIs was used as the reference standard for hepatic fat content.

### Image assessment

The images obtained during the study have been saved as image files. The evaluators will be required to assess the level of hepatic steatosis without any clinical data. After deliberation and achieving a consensus, the evaluators will complete the case report forms (CRFs). Subsequently, the study coordinators shall gather all images and CRFs for specialized storage within the database.

### Primary endpoint

In this study, the primary endpoint seeks to evaluate the efficacy of QUS techniques assessing hepatic steatosis, utilizing MRI-PDFF as the gold standard, compared to anthropometric measurements, laboratory assessments and other imaging methods before and after bariatric surgery. Success in this endeavor would be measured by the ability of QUS techniques to better evaluate the degree of hepatic steatosis as compared to other methods, thereby providing diagnostic improvement beyond current practice. Such results would signify the feasibility of using QUS techniques for postoperative evaluation of bariatric surgery.

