### Sample size

To ensure accurate evaluation of QUS techniques for hepatic steatosis grading, it is imperative to calculate the required sample size. Assuming an 80% MAFLD prevalence in the target population and 80% sensitivity and 90% specificity in QUS techniques, we calculated the minimum number of subjects needed to be 75 using a paired non-parametric test in the non-parametric module of PASS. Considering factors like data loss, cases “lost to follow-up”, our study will involve 100 patients scheduled to undergo RYGB.

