### Data analysis

The statistical analysis for this study will be performed using the SAS 9.2 software package (SAS Analytics, Marlow, UK) and R (v4.3.1; R Core Team), which is widely available for commercial use. The significance level has been predetermined to be 0.05 for all two-sided tests. The mean and standard deviation will be used to express normally distributed quantitative data.

To compare quantitative data, a paired t-test will be employed. Meanwhile, categorical variables will be analyzed using the chi-squared test. Pearson correlation coefficients will be utilized to evaluate the relationship between QUS parameters and other factors under consideration. Univariable linear regressions of QUS and other methods on MRI-PDFF were conducted to calculate the adjusted linear correlation coefficient (r). Then receiver operating characteristic (ROC) curves of QUS and other methods for the detection of MRI-PDFF ≥5% and ≥10% were plotted. The best cut-off values were defined as the cut-off values corresponding to the maximum Youden indexes.

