**Figure 3 F3:**
[figure not shown]
Quantitative analysis of liver fat in an obese Chinese male. Based on B-mode ultrasound image, the color-coded maps of TAI map (**A**) reflecting center frequency and TSI map (**B**) reflecting Nakagamia parameters are generated. (**C**) MRI-PDFF values were 14.72%.

The average BMI of all participants was 26.43, which meets the diagnostic criteria for overweight. More than 50% of patients (15/21, 71.43%) presented with symptom of right upper abdominal distension. For the value of MRI-PDFF, the average was 13.86%. MRI results from eight patients were below 10%. For MRI-PDFF ≥10%, a total of 13 patients were in this category (13, 62.9%).

All the data were analyzed in R (v4.3.1; R Core Team). A two-sided *P* < 0.05 was considered statistically significant. AC-TAI showed moderate correlations with MRI-PDFF (adjusted *r* = 0.632; *P* < 0.05). Linear correlation between SC-TSI and MRI-PDFF was not significant (*P* = 0.982) (Table 1). For MRI-PDFF ≥10%, SC-TSI showed moderate correlations with MRI-PDFF (adjusted *r* = 0.677; *P* < 0.05) (Figure 4). In a way, the results signified the feasibility of using QUS techniques for postoperative evaluation of bariatric surgery.

**Table 1 T1:** Linear regression between AC-TAI/SC-TSI and other parameters.

Parameters	AC-TAI		SC-TSI	
	Adjusted R	*P*-value	Adjusted R	*P*-value
CAP	0.578	<0.05	0.343	0.070
MRI-PDFF	0.632	<0.05	0.229	0.982

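### Primary success is stated for QUS techniques as a group, without saying whether AC-TAI, SC-TSI or both must succeed, so a split result could be reported as success for both

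*Protocol article*

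**What the plan says.** The Primary endpoint section defines the target: "the primary endpoint seeks to evaluate the efficacy of QUS techniques assessing hepatic steatosis, utilizing MRI-PDFF as the gold standard". Its success criterion is "Success in this endeavor would be measured by the ability of QUS techniques to better evaluate the degree of hepatic steatosis" compared with the other methods, and the inference attached to success is "Such results would signify the feasibility of using QUS techniques for postoperative evaluation of bariatric surgery". Neither parameter is named there. The O (outcome or objective) section and the closing Conclusion also speak of QUS techniques as a group.

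The QUS techniques section is specific: "Two QUS parameters, namely AC-TAI and SC-TSI, were calculated from the RF data". The Introduction explains that they capture different things: AC-TAI reflects attenuation, and SC-TSI reflects the concentration and arrangement of scatterers. The Data analysis section describes univariable regressions on MRI-PDFF and ROC curves, with no combined score. The Sample size section assumes "80% sensitivity and 90% specificity in QUS techniques", without saying whether this applies to each parameter.

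For SC-TSI in the pilot, the Results section says: "Linear correlation between SC-TSI and MRI-PDFF was not significant" (P = 0.982). It then reports a positive SC-TSI result in patients with MRI-PDFF ≥10% and concludes: "In a way, the results signified the feasibility of using QUS techniques for postoperative evaluation of bariatric surgery".

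**The concern.** Two different index tests share one success statement and one conclusion. With no composite defined, no single quantity called QUS exists that can beat the comparators; only AC-TAI or SC-TSI can. If one succeeds and the other does not, the wording gives no rule for the verdict and leaves room to announce success for the group.

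At stake is an endorsement for postoperative use of a parameter that did not perform against MRI-PDFF in the trial's own data. A centre measuring only that parameter would be relying on a claim earned by the other. The pilot is a worked example of a split result over the whole sample that ended in a collective verdict.

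**Working it through.** **1. The unit of claim against the unit of analysis.**

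| Section | Unit |
|---|---|
| Primary endpoint: success and inference | QUS techniques, collectively |
| QUS techniques: measurement | AC-TAI and SC-TSI, separately |
| Data analysis: regressions, ROC | one predictor at a time, no composite |
| Results, Table 1 | one column per parameter |
| Results, Discussion, Conclusion: verdict | QUS techniques, collectively |

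The analysis yields two answers and the success statement allows for one. No sentence says how the two become one.

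**2. What the pilot showed for each parameter.** Inputs are from Results and Table 1: n = 21; AC-TAI adjusted r = 0.632; SC-TSI adjusted R = 0.229 with P = 0.982; SC-TSI in the ≥10% subset (n = 13) adjusted r = 0.677. For one predictor, R² = 1 − (1 − adjusted R²)(n − 2)/(n − 1), and r is tested by t on n − 2 degrees of freedom.

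- *AC-TAI, n = 21.* Adjusted R² = 0.632² = 0.399. R² = 1 − 0.601 × 19/20 = 0.429, so r = 0.655 and P = 0.001. This agrees with the printed P < 0.05.
- *SC-TSI, n = 21, 0.229 read as an ordinary positive value.* Adjusted R² = 0.052, R² = 0.100, r = 0.316, P = 0.16. This does not agree with the printed 0.982.
- *SC-TSI, n = 21, worked back from P = 0.982.* R² = 0.00003, so |r| = 0.005. Adjusted R² = 1 − (1 − 0.00003) × 20/19 = −0.0526, and √0.0526 = 0.229, the printed value. The 0.229 therefore appears to be the root of a negative adjusted R² with its sign dropped, and the correlation is about 0. Fisher 95% interval: tanh(0.005 ± 1.96/√18) = −0.43 to 0.44.
- *Check of the method.* In the SC-TSI/CAP row, 0.343 gives P = 0.071; the table prints 0.070.
- *SC-TSI, ≥10% subset, n = 13.* Adjusted R² = 0.458. R² = 1 − 0.542 × 11/12 = 0.503, so r = 0.71 and P = 0.007.

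Over the whole sample, then, AC-TAI explains about 43% of the variance in MRI-PDFF and SC-TSI about none. The verdict covered both. The abstract gives the SC-TSI subset result and omits the whole-sample null.

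**3. What the choice of rule implies.** The Data analysis section says: "The significance level has been predetermined to be 0.05 for all two-sided tests". The figures below are illustrative, because the article states neither power nor the correlation between the two tests.

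- *Either parameter suffices.* If neither truly differs from the comparator, the chance of at least one significant two-sided test is 1 − 0.95² = 9.75% when independent, and 9.1% at an assumed correlation of 0.5. Counting only results in favour of QUS, it is 1 − 0.975² = 4.9% when independent.
- *Both must succeed.* No split of the significance level is needed. With independent tests, joint power is 0.80² = 64% if each has 80%, and 0.90² = 81% if each has 90%.

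**The case against.** A reader might infer that a win by one parameter automatically validates the other. The article does not say so. The plural wording fits a rule that both must succeed equally well, and under that rule the harm does not arise. This objection stands: the fault is an open rule, not a stated either-suffices rule.

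A reader might also infer that the pilot carried SC-TSI on AC-TAI's result alone. It did not. The Results section credits SC-TSI with its own finding in the ≥10% group, prints the whole-sample null, and hedges the conclusion. That also stands, but the support is weak. The subset has 13 patients chosen on the reference standard, so it cannot show detection at the 5% or 10% cut-offs in the Data analysis section. Nor does it speak to livers with little fat after surgery, and the Discussion cites a bypass cohort in which steatosis disappeared in 84%.

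The pilot does not show that SC-TSI fails. Its interval admits a moderate correlation, and its participants had suspected NAFLD with a mean BMI of 26.43, whereas the trial requires BMI ≥ 27.5 and planned RYGB. The single 80%/90% assumption is not evidence of pooling either, since it can apply to each parameter.

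Finally, multiplicity and detailed decision rules may sit in an analysis plan that is not shown. That is fair, and their absence is not the point. The unit of the primary claim is fixed in the Primary endpoint section itself.

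**Conclusion.** The point holds as a defect in how the primary claim is worded. Success and conclusion are fixed for QUS as a group, the two parameters are measured and analysed apart, and the one-or-both question is left open. A split result could therefore be announced as success for both; the text does not make that certain.

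The pilot illustrates the size of a possible split: r = 0.655 for AC-TAI against about 0 for SC-TSI in the same 21 people, followed by a collective verdict. The SC-TSI value is inferred from its P-value and rests on reading 0.229 as the root of a negative adjusted R²; the printed P = 0.982 points to near zero in any case. The conclusion does not depend on the sample size of 75 or on any assumed power. The change should be made, because it decides what the trial may conclude.

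**What to change.** - In O (outcome or objective), Primary endpoint and Conclusion, state that AC-TAI and SC-TSI are each judged separately against MRI-PDFF and the comparators, and that the conclusion names only the parameter that succeeded. A claim for QUS techniques as a whole requires both to succeed.
- In Sample size, state that the 80% sensitivity and 90% specificity are assumed for each parameter.

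**Cost.** Both parameters are already measured and analysed separately, so no visits or data are added. A mixed result can no longer be reported as success of QUS as a whole, and the claim for both has lower power than either single claim (64% or 81% in the illustration above; higher if the tests are positively correlated). If the sponsor also chooses to split the significance level at 0.025 each, the change is more than wording. Had 75 subjects given 80% power (an assumption), power per parameter would be 71%, and about 91 evaluable subjects would be needed to restore it. That is fewer than the 100 to be enrolled, but more than the 75 that remain after the plan's own allowance for losses.

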### I (intervention)

All patients will receive anthropometric measurements (BMI, waist circumference, hip circumference), blood-based biochemical analyses (alanine aminotransferase ALT, aspertate aminotransferase AST, γ-glutamine transferase γ-GTP, total cholesterol Tc, triglyceride, high-density lipoprotein cholesterol HDL-c, low-density lipoprotein cholesterol LDL-c), ultrasonic examination (B-mode US, CAP, TAI, TSI) and magnetic resonance imaging proton density fat fraction (MRI-PDFF) before and 1, 3, 6, 12 months after bariatric surgery.

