### C (comparison or control)

Our research constitutes a prospective superiority trial, wherein self-control and blind map-reading served as key components. The study was conducted within a single-center and aimed to assess the efficacy of QUS techniques compared to other imaging methods, anthropometric measurements, and laboratory assessments which were designated as control groups.

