### Schedule of the study

Upon securing informed consent, the cohort shall meticulously evaluate the criteria for inclusion and exclusion as well as background information pertaining to each participant. It is noteworthy that a total of 104 cases were scrutinized in this study, consisting of 100 formal cases and four training cases, which were consecutively incorporated into the analysis. All participants will receive anthropometric measurements (BMI, waist circumference, hip circumference), blood-based biochemical analyses (ALT, AST, γ-GTP, Tc, Triglyceride, HDL-c and LDL-c), ultrasonic examination (B-mode US, CAP, TAI, TSI) and MRI-PDFF.

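### The success rule is that QUS is better than other methods, but the stated analysis includes no test of the difference in accuracy between two methods and names no primary contrast

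*Protocol article*

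**What the plan says.** Under C (comparison or control), the protocol article states "Our research constitutes a prospective superiority trial" and says that it "aimed to assess the efficacy of QUS techniques compared to other imaging methods, anthropometric measurements, and laboratory assessments". Under Primary endpoint, with MRI-PDFF as gold standard, success is "measured by the ability of QUS techniques to better evaluate the degree of hepatic steatosis as compared to other methods". The aim covers the time before surgery and the time after it.

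The Data analysis section gives the following methods:
- a paired t-test for quantitative data and a chi-squared test for categorical data;
- Pearson correlations of the QUS parameters with other factors;
- univariable regressions of each method on MRI-PDFF;
- ROC curves, described as "receiver operating characteristic (ROC) curves of QUS and other methods for the detection of MRI-PDFF ≥5% and ≥10% were plotted";
- cut-offs at the maximum Youden index.

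On error control it says only "The significance level has been predetermined to be 0.05 for all two-sided tests".

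The Sample size section arrives at a minimum of 75 from a paired, non-parametric procedure in PASS. It assumes 80% prevalence, 80% sensitivity and 90% specificity for QUS. The procedure is not named, and the Data analysis section does not mention it.

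**The concern.** A claim of superiority in accuracy needs a test of a difference: between two AUCs, two sensitivities or two correlations with MRI-PDFF, allowing for both methods being measured in the same patients. The listed methods do not provide one. The paired t-test compares means. AC-TAI, CAP, BMI and ALT are in different units, so a difference in means says nothing about which follows liver fat more closely. The correlations, regressions and ROC curves describe each method by itself.

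The success rule also leaves open which QUS parameter, comparator, threshold and visit decide the matter, and whether QUS must beat one comparator or all of them. A larger observed r or AUC is not evidence of superiority, and a contrast picked after the results are seen has no controlled error rate. The study's main conclusion is at stake.

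**Working it through.** **1. Stated methods against the success rule**

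| Listed method | What it answers | Tests a difference in accuracy? |
|---|---|---|
| Paired t-test | Do two means differ? | No |
| Chi-squared test | Are categories associated? (no paired version named) | No |
| Pearson r, univariable regression | How closely does one method follow PDFF or another factor? | No |
| ROC curves, Youden cut-offs | How does one method classify PDFF status? | No; the curves are plotted, not compared |

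The minimum of 75 cannot be reproduced from the stated inputs, because comparator accuracy, discordance and power are not given. It therefore does not reveal which paired test was meant. That is a separate point, and the present one does not depend on it.

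**2. How many contrasts are open**

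Inputs from the article:
- QUS parameters: 2 (QUS techniques: "Two QUS parameters, namely AC-TAI and SC-TSI, were calculated from the RF data").
- Comparators (listed under I (intervention)): 3 anthropometric (BMI, waist, hip) + 7 laboratory (ALT, AST, γ-GTP, Tc, triglyceride, HDL-c, LDL-c) + 2 imaging (B-mode, CAP) = 12.
- Level: 0.05 two-sided for each test.

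At one visit and one threshold there are 2 × 12 = 24 contrasts. If any win counts, all nulls are true and the tests are independent:
- at least one P < 0.05 in either direction: 1 − 0.95^24 = 0.71;
- at least one in favour of QUS: 1 − 0.975^24 = 0.46.

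The contrasts share patients and the reference standard, so they are correlated and the true figures are lower.

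**3. How large a chance gap in AUC can be**

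Assumptions:
- N = 75 with 80% prevalence, so 60 diseased and 15 not. The 80% is the article's MAFLD figure, used here as a stand-in for PDFF status.
- AUC 0.861, the value that the Discussion reports for AC-TAI at PDFF ≥5% from a cited study.
- A comparator AUC of 0.80 (assumed).
- Correlation ρ between the two AUC estimates of 0.3 to 0.7 (assumed).

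Hanley-McNeil variance, with Q1 = A/(2 − A) and Q2 = 2A²/(1 + A):

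SE² = [A(1 − A) + 59(Q1 − A²) + 14(Q2 − A²)] / (60 × 15)

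- A = 0.861: Q1 = 0.7559, Q2 = 0.7967, SE = 0.044.
- A = 0.80: Q1 = 0.6667, Q2 = 0.7111, SE = 0.055.

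For the paired difference, SE_d² = 0.0442² + 0.0551² − 2ρ(0.0442)(0.0551):

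| ρ | SE_d | 95% half-width (1.96 × SE_d) |
|---|---|---|
| 0.3 | 0.059 | 0.12 |
| 0.5 | 0.051 | 0.10 |
| 0.7 | 0.040 | 0.08 |

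The gap in this example is 0.861 − 0.80 = 0.061, which is smaller than every half-width in the table. QUS could rank first by this margin with an interval that includes zero.

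**The case against.** The strongest reply is that this is a journal article. A statistical analysis plan may name a DeLong or McNemar test, a primary contrast and a multiplicity rule, and nothing in the article says that superiority will be declared by ranking. The Sample size section also shows that a paired comparison was envisaged. Part of this stands: test names and adjustment details are normally left to the analysis plan, and an intention to rank is not stated. But the article itself fixes a superiority rule, a list of methods that cannot test it, and 0.05 for every two-sided test. It sizes the study on a paired procedure that its own analysis section does not carry forward. Those parts do not fit together as printed.

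A reader might multiply everything out (2 × 12 × 2 thresholds × 5 visits = 240) and infer 240 tests with about 12 false positives. The documents do not support that. The article plans no such set of tests and does not say that ROC curves are drawn at each visit. The count of 12 needs every null to be true, including QUS being no more accurate than LDL-c or hip circumference. If success means beating all comparators, having 12 of them does not inflate the type I error at all. The article does not say which reading applies, and that ambiguity is the fault.

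A reader might also judge chance gaps from the half-width of a single AUC (0.09 to 0.11 here). The paired difference is the relevant quantity. Its range is similar but depends on an assumed correlation.

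**Conclusion.** The point holds. The stated analysis cannot test the stated success rule, and no contrast is named on which superiority would be decided. Followed as written, the conclusion would rest on separate r and AUC estimates or on a contrast chosen later.

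The 71% figure is an upper illustration. It applies only if any win counts, all 24 nulls are true and the tests are independent. The half-width of about 0.08 to 0.12 rests on the assumed 60/15 split, AUCs and correlation. The split may be quite different for PDFF ≥10% or after surgery, where the Discussion cites high rates of regression. The finding itself comes from comparing the sections and needs none of these assumptions. It should be corrected before analysis, because it concerns the primary endpoint.

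**What to change.** Before any analysis, amend the protocol and analysis plan as follows.

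1. Name the primary contrast in full: QUS parameter, comparator, PDFF threshold and visit. One example is AC-TAI versus CAP for PDFF ≥5% before surgery. Test the same contrast at 12 months next, in fixed sequence and only if the first succeeds, so that the before-and-after aim is kept. The choice of parameter belongs to the investigators. The pilot favours AC-TAI, but it had 21 patients with mean BMI 26.43, below the entry limit of 27.5. The cited study favours SC-TSI (AUC 0.964 against 0.861).
2. Test it with a paired DeLong test or a patient-level bootstrap at two-sided 0.05. Success means that the lower 95% limit of the AUC difference exceeds 0.
3. If correlations with MRI-PDFF are compared, use a test for dependent correlations.
4. Report all other contrasts with confidence intervals, as descriptive or Holm-adjusted.
5. Keep N at 100, but state that the 75 was not derived for this test and give the AUC difference that can be detected.

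The cost is revised wording, a short detectable-difference calculation and a little code; no new data are needed. Fewer contrasts can be called significant, and power may be modest. As an illustration, with 80 diseased and 20 not, AUC 0.90 versus 0.80 and a correlation of 0.3 to 0.7 (all assumed), power is about 54% to 84%. Losses to follow-up would reduce it for the 12-month contrast.
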